## Abstract

**Background:**

Patients undergoing chemotherapy are highly burdened by side effects. These may be caused by the pharmacodynamics of the drug or be driven by psychological factors such as negative expectations or pre-conditioning, which reflect nocebo effects. As such, negative pre-treatment expectations or prior experiences might exacerbate the burden of chemotherapy side effects. Educating patients about this nocebo effect has been put forward as a potential strategy to optimize patients’ pre-treatment expectations. In this study, we evaluate whether a briefing about the nocebo effect is efficacious in reducing side effects.

**Methods:**

In this exploratory study, a total number of *n* = 100 outpatients with newly diagnosed gastrointestinal cancers are randomized 1:1 to an information session about the nocebo effect (nocebo-education) or an attention control group (ACG) with matching interaction time. Assessments take place before the intervention (T1 pre), post-intervention (T1 post), and 10 days (T2) and 12 weeks (T3) after the initial chemotherapy. The primary outcomes are the patient-rated number and intensity of side effects at 10-days and at 12-weeks follow-up. Secondary outcomes include coping with side effects, tendency to misattribute symptoms, compliance intention, attitude towards the chemotherapy, co-medication to treat side effects and the clinician-rated severity of toxicity. Further analyses are conducted to investigate whether a potential beneficial effect is mediated by a change of expectations before and after the intervention.

**Discussion:**

Informing patients about the nocebo effect might be an innovative and feasible intervention to reduce the burden of side effects and strengthen patients’ perceived control over adverse symptoms.

**Trial registration:**

The trial is registered at the German Clinical Trials Register (ID: DRKS00009501; retrospectively registered on March 27, 2018). The first patient was enrolled on September 29, 2015.

## Background

Gastrointestinal tumors, including cancer of the esophagus, stomach, colon, rectum, anus, pancreas, gallbladder and bile duct, constitute the largest group of cancer for men, and the second largest group of cancer for women [1]. Further, they are characterized by high mortality rates [1]. One of the treatment options for gastrointestinal tumors is chemotherapy, which can be indicated in the neoadjuvant, adjuvant or palliative setting [2]. Due to the high toxicity of the chemotherapy, cancer patients are commonly burdened by side effects of varying severity which may impair quality-of-life [3, 4]. Furthermore, side effects have substantial weight in the individual decision process of whether or not to proceed with chemotherapy and were shown to be one of the three major predictors of treatment discontinuation in the palliative setting [5, 6]. Strikingly, side effects are not fully defined by the pharmacodynamics of a given drug, but can also be caused by psychological factors. These so-called nocebo effects are best known as the counterparts of placebo effects [7]. The nocebo effect can depend on a variety of factors, e.g. the patient-practitioner relationship, a patient’s treatment expectations, or prior learning experiences [8]. Nocebo-driven side effects can occur as unspecific side effects, i.e. symptoms not explainable by the drug, or may also exacerbate specific side effects [9]. Studies which investigated adverse events after placebo intake [10, 11], as well as studies which used verbal suggestions to manipulate treatment expectations prior to medication intake, demonstrated the existence of nocebo effects [12–14].

One of the main underlying mechanisms for the development of nocebo effects is expectations. These are formed based on prior experiences (either specific to the treatment or in general, to medical procedures) [15], social learning [16], and the information received about the treatment [17].

In clinical practice, patients are briefed about the treatment including potential risks in the informed consent. Although a great achievement towards patient autonomy, standard informed consent procedures may facilitate negative expectations which can, in turn, cause nocebo effects [18]. As reported in a meta-analysis, negative pre-treatment expectations predict the occurrence of actual side effects [19]. The strongest associations between symptom expectation and symptom occurrence were found for pain, fatigue, and nausea [19]. Moreover, negative treatment expectations prior to chemotherapy are high. In a study by Hofman and colleagues [20], most of the cancer patients expected that they would develop severe or long-lasting side effects such as fatigue (90.6%) and nausea (78%). In summary, optimizing informed consent procedures may be an essential module in the prevention of nocebo effects during chemotherapy.

By acknowledging the ethical and legal necessity of informed consent on the one side and the importance to minimize risks on the other, Barsky and colleagues [21] suggested educating patients about the nocebo effect. When aware of the existence of expectation-induced nocebo effects, patients’ risk of misattributing unspecific symptoms to the treatment may be lower and they may be less vigilant to bodily signals, which again, may decrease the number and intensity of symptoms [22]. First evidence has shown that informing participants about the nocebo effect led to a reduction of symptoms that were allegedly caused by wind turbines [23]. Despite the high relevance of preventing nocebo effects during routine chemotherapy treatments, no comparable research has yet been conducted in the clinical context.

The primary aim of this exploratory clinical trial is to investigate the effects of a nocebo-education on the patient-rated number and intensity of side effects in gastrointestinal cancer patients undergoing chemotherapy. By suggesting that side effects are not thoroughly determined by the pharmacodynamics of the treatment, patients’ perceived self-efficacy to control side effects may be increased, and the misattribution of ambiguous body signals to the treatment may be reduced. Additionally, the nocebo-education may also facilitate the development of positive expectations in general, which in turn, can improve health outcomes [24]. Thus, we will investigate, as secondary outcomes, patients’ perceived coping with side effects, tendency to misattribute symptoms, compliance intention, attitude towards the chemotherapy, clinician-rated severity of toxicity and type of co-medication used to treat side effects. Furthermore, we will examine whether optimized treatment expectations mediate the hypothesized beneficial effects of the nocebo-education. Since monitoring information coping styles have been associated with a higher report of side effects [25], we will investigate treatment information seeking as a moderator.

## Methods

### Study design

The RENNO trial (German Acronym for “**R**eduzierung des subjektiven **E**rlebens von **N**ebenwirkungen während der Chemotherapie durch Aufklärung über den **No**cebo-Effekt”) is a randomized-controlled, single-site superiority trial with two parallel arms and a primary endpoint of patient-reported number and intensity of side effects at 10 days and 12 weeks after the first chemotherapy session. Patients with newly diagnosed gastrointestinal cancers scheduled for chemotherapy are block-randomized 1:1 to a nocebo-education group or an attention control group entailing a quality-of-life interview.

The intervention takes place < 24 h before chemotherapy commences or during the administration of the first dose. Measurements are taken before (T1-pre), and after the intervention (T1-post), and 10 days (T2) and 12 weeks (T3) after the initial chemotherapy (Table 1).

**Table 1 Tab1:** Schedule for enrolment, interventions and assessments

Time points	Study period				
	Allocation	Post-allocation			
	t_1pre_	t_1_	t_1post_	t_2_	t_3_
ENROLMENT					
Eligibility screen^a^	✓				
Informed consent	✓				
Randomized assignment	✓				
INTERVENTIONS					
Nocebo-education group		✓			
Attention control group		✓			
ASSESSMENTS					
Baseline variables					
Demographic and medical characteristics	✓				
Distress Thermometer	✓				
Information coping style	✓		✓		
Outcome variables					
Side effect number and intensity (GASE)^b^				✓	✓
Coping with side effects (GASE-Coping)				✓	✓
Misattribution of symptoms (GASE-Attribution)				✓	✓
Co-medication to treat side effects (yes/no)				✓	✓
Compliance intention	✓		✓	✓	✓
Attitude towards the chemotherapy	✓		✓	✓	✓
Severity of toxicity (CTC)^c^	✓			✓	✓
Further variables					
Expected side effects (GASE-Expect)	✓		✓		
Expected coping with side effects (GASE-Coping Expect)	✓		✓		
Expected efficacy of chemotherapy			✓		
Relevance of the conversation			✓		
Knowledge about the nocebo effect^d^			✓	✓	✓
Disease progression				✓	✓

*Note.* The time points T1-pre and T1-post refer to the intervention whereas the T2 and T3 refer to the chemotherapy (10 days and 12 weeks after the initial chemotherapy). *GASE* Generic Assessment of Side Effects, *CTC* Common Toxicity Criteria

^a^The eligibility screening takes place in two steps. In the first step, medical eligibility criteria are checked, whereas in the second step, all further criteria are assessed as part of the health professional-patient communication right before the signing of the informed consent

^b^Assessed symptoms include fatigue, nausea, diarrhea, vomiting, headache, shortness of breath, and rash

^c^Severity of toxicity is assessed by the clinician at every cycle

^d^Knowledge about the nocebo effect is only assesses in the nocebo education group

### Trial registration and ethical approval

Ethics approval has been given by the local ethics committee of the University of Hamburg. The trial has been retrospectively registered on March 27th, 2018 at the German Clinical Trial Register (ID: DRKS00009501).

### Study sample

Patients with newly diagnosed cancer of the gastrointestinal tract, including the esophagus, stomach, colon, rectum, anus, pancreas, gallbladder and bile duct who are indicated for chemotherapy are eligible for this study. Chemotherapy can be given in the adjuvant, neoadjuvant, or first-line palliative setting, and is administered as a mono chemotherapy or combination-chemotherapy, with or without vascular endothelial growth factor (VEGF)-antibody. To enroll, patients must be at least 18 years old, have no difficulties understanding German, and be able to give informed consent. Exclusion criteria include the following: any chemotherapy before trial inclusion, limited capability of self-care (Eastern Co-operative Oncology Group (ECOG) ≥ 3 [26]), severe comorbid psychological disorder (schizophrenia, substance abuse, severe depression or severe anxiety disorder), concurrent psychotherapeutic or psychopharmacological treatments, life-threatening comorbid medical condition, diagnosis of chronic skin disease, dyspnea, or chronic lung diseases due to its interference with chemotherapy side effects, indication for epidermal growth factor receptor (EGFR)-antibody treatment since it may cause acne-like rash. Since prior research has found that the link between negative treatment expectations and side effects was more pronounced among patients who had chemotherapy experience [19], we excluded patients with prior chemotherapy experience, including having received the first dose before enrolment, to achieve an increased homogeneity of the sample.

### Recruitment

Patients are recruited from the University Medical Center (UMC) Hamburg-Eppendorf, Department of Oncology, Hematology and Bone Marrow Transplantation and from cooperating practices. All patients are treated in an outpatient setting. With the aim to achieve adequate enrolment of participants, each patient with a newly diagnosed gastrointestinal cancer treated at the Department of Oncology of the UMC is screened. The first screening of inclusion criteria is conducted by the patient’s treating oncologist.

The healthcare professional (medical doctoral candidate or Psychologist, B.Sc.) informs patients about the study’s aim (“gaining an enhanced understanding of the quality-of-life of patients which undergo chemotherapy including potential worries and expectations about the treatment”) and procedures (“assignment to one of two possible conversations”). Further eligibility criteria are assessed through the healthcare professional by inquiring the patient directly (e.g. ECOG score). Informed consent is obtained by the same healthcare professional prior to enrolment.

### Randomization and blinding

A stratified block randomization is performed after the signing of the informed consent. To prevent a potential selection bias due to predictability, the block sizes are not noted here. The stratum distress is assessed at T1-pre using a distress-thermometer, a commonly used screening instrument among oncological patients ranging from 0 (not distressed) to 10 (extremely distressed) [27]. The allocation sequence for each stratum category (distress < 5 ‘low’ vs. distress ≥5 ‘high’) is produced by a research assistant prior enrolment using a computer program [28]. Sequentially numbered, opaque, sealed envelopes are used for the concealment of group assignment. Randomization is performed by a trained healthcare professional who, according to the distress level indicated by the patient, draws the envelope from the respective box. Patients are present during the allocation and are informed about their assignment instantaneously.

Due to the nature of the study, patients are not blinded. However, they are unaware of the specific study hypotheses and the content of the intervention that they do *not* receive. The trained healthcare professional is not blinded to group assignment. However, we aimed to confine the post-randomization interaction between the trained healthcare professional and the patient to the intervention. Follow-up assessments are conducted independently via mail using a standardized cover letter, i.e., no further interactions take place. Only in cases when patients do not complete assessment, the healthcare professional conducts a reminder call which is manualized in advance.

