### Sample size calculation

In a pilot study which aimed to validate the nocebo-education session, we found a moderate to large effect (*Cohen’s d* = 0.50–0.65) when comparing post-session side effect expectations between participants who were educated vs. those who were not educated. Since no prior study has been conducted to examine the effect of a nocebo education on side effects, we used the aforementioned effect size of side effect expectations as a proxy for actual side effects. Hence, when conducting an independent *t*-test, given an effect size of *d* = 0.60, the desired power of 80%, and an alpha-error of 0.05 (two-tailed testing), we obtained a required sample size of *N* = 45 per group for this exploratory clinical study. When accounting for a dropout rate of 10%, a total sample of *N* = 100 is needed to investigate potential group differences with adequate power for our primary outcome burden of side effects.

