### Statistical methods

All outcome analyses will be conducted for the intention-to-treat sample. Missing values will be imputed using the expectation-maximization algorithm. We will conduct ANCOVA for the primary outcomes number and intensity of side effects, and for the secondary outcomes coping with side effects, tendency to misattribute symptoms, compliance intention, attitude towards chemotherapy, and medical toxicity at both time points (10 days and 12 weeks) with adjustments for the stratum distress and for cancer staging. Logistic regression will be conducted for the secondary outcome co-medication to treat side effects with the same set of covariates. The T1-pre to T1-post changes in expected side effects and expected coping with side effects will be examined as mediators of the effect of group on the outcomes. Exploratory analyses will be conducted to compare the expected efficacy of the chemotherapy between groups using independent t-tests.

Moderate analyses will be carried out by including the group x information coping style interaction in the ANCOVA. Sensitivity analyses will be conducted under exclusion of (1) patients of the nocebo-education group who either indicated to not have heard about the nocebo effect or who gave a wrong description and (2) patients with tumor progression.

No interim analyses will be conducted.

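### Adjusting for distress as a low/high stratum is valid, but adding the already recorded 0-10 score would be modestly more efficient in the ANCOVAs

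*Protocol article*

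**What the plan says.** Under Randomization and blinding, distress is measured before the intervention on a thermometer "ranging from 0 (not distressed) to 10 (extremely distressed". Allocation sequences are prepared separately for two categories, "distress < 5 ‘low’ vs. distress ≥5 ‘high", and the patient's score decides which box the envelope is drawn from.

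Under Statistical methods, the ANCOVAs for the primary and secondary outcomes are run "with adjustments for the stratum distress and for cancer staging". The logistic model for co-medication takes the same covariates. The coding of distress in these models is not spelled out. The two-level category is the natural reading, but the randomisation section also says "The stratum distress is assessed at T1-pre using a distress-thermometer", which ties the same phrase to the thermometer reading.

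Table 1 schedules the patient-rated number and intensity of side effects only at T2 and T3, so the primary outcomes have no baseline value to adjust for.

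**The concern.** As a two-level factor, distress treats a score of 0 like a 4 and a score of 5 like a 10. If side effects rise roughly in line with distress, the variation within each stratum stays in the residual although the data to remove it are already held.

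This carries somewhat more weight here than in most trials. ANCOVA usually draws most of its precision from the baseline value of the outcome, and here there is none. Distress and cancer staging are the only planned covariates. The planned sample has little slack at the assumed effect size (80.4% power, shown below). What is at stake is the width of the intervals for the ANCOVA outcomes. Bias and type I error are not affected.

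**Working it through.** **Inputs from the protocol article.** Thermometer 0 to 10 and the cut at 5 (Randomization and blinding). Sample size from "when conducting an independent *t*-test", "given an effect size of *d* = 0.60, the desired power of 80"%, "an alpha-error of 0.05 (two-tailed testing"), giving 45 per group and 100 in total after 10% dropout (Sample size calculation).

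**Inputs that are assumptions.** The article does not give the distribution of distress, the share of patients in the high stratum (p) or the correlation r between distress and the outcome. I take p = 30% to 50% and r = 0.1 to 0.5.

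**Step 1: the plan's own figure.** The exact two-sample t-test at d = 0.60 needs 44.6 per group, rounded up to 45. Power at 45 is 80.4%. 90 / 0.90 = 100. The stated sample size reproduces, and it counts on no gain from any covariate.

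**Step 2: share of explainable variance kept by the cut.** For a normal score and a linear relation, the share kept is k = φ(z)² / [p(1 − p)], where z is the cut point on the standard normal scale.

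- p = 0.50: φ(0) = 0.399, k = 0.159 / 0.25 = 0.637, so 36% is lost.
- p = 0.30: φ(0.524) = 0.348, k = 0.121 / 0.21 = 0.576, so 42% is lost.

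On the 0-10 integer scale cut at 5, other assumed shapes give different losses:

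- bell-shaped, underlying mean 3 to 6 and SD 2 to 3: about 31% to 45%
- bell-shaped, underlying mean 7: 40% to 59%
- uniform: 25%
- one U-shaped example: 16%

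These are shares of r², not of outcome variance. At r = 0.3 the score explains 9.0% of outcome variance, and the two-level form explains 0.637 × 9.0% = 5.7% or 0.576 × 9.0% = 5.2%.

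**Step 3: residual variance and power.** Residual variance with the score relative to the stratum alone is (1 − r²) / (1 − k r²). Power is for d = 0.60 and 45 per group, with the residual SD scaled by √(1 − r²) or √(1 − k r²). Ranges run from p = 50% to p = 30%.

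| r | Further fall in residual variance | Power, stratum only | Power, with score |
|---|---|---|---|
| 0.1 | 0.4% | 80.6% | 80.8% |
| 0.2 | 1.5% to 1.7% | 81.4% to 81.3% | 81.9% |
| 0.3 | 3.5% to 4.0% | 82.6% to 82.4% | 83.9% |
| 0.4 | 6.5% to 7.5% | 84.4% to 84.0% | 86.7% |
| 0.5 | 10.8% to 12.4% | 86.6% to 86.0% | 90.2% |

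Expressed as patients on 90: 90 / 0.965 − 90 ≈ 3 at r = 0.3 and p = 50%; 90 / 0.876 − 90 ≈ 13 at r = 0.5 and p = 30%.

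**Step 4: allow for the cost of the extra term.** Step 3 ignores the degree of freedom spent. A simulation with 90 patients, a normal score, and the stratum indicator and one staging covariate already in the model gave these ratios of treatment-effect variance, with the score against without it: about 1.01 at r = 0, 1.00 at r = 0.15, just under 1.00 at r = 0.2, and 0.97 to 0.98 at r = 0.3. Break-even therefore lies a little below r = 0.2.

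**The case against.** The strongest reply is that nothing here is wrong. Adjusting for the factor used to stratify the randomisation is a valid analysis that follows the design, and the sample size relies on no covariate gain. That stands, and it limits the point to an efficiency suggestion.

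Second, the wording does not exclude the 0-10 score. If the score is what the plan means, most of the point falls away and only the need to state the coding remains. That also stands: the two-level form is the likely reading, not a certain one.

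Third, a reader might infer a fixed loss of some 40% of the information in distress. The documents do not support a single figure. It needs a near-normal score, a linear relation and a particular split, none of which the article gives.

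Fourth, a reader might infer narrower intervals for every outcome at no cost. This fails twice. When distress is weakly related to the outcome, the extra term gains nothing or loses slightly. In the logistic co-medication model, a prognostic covariate tends to raise the standard error of the treatment log odds ratio and also changes what is estimated. Simulations with 90 patients and assumed log-odds slopes of 0.3, 0.6 and 1.0 per SD of distress gave median standard errors rising from 0.437 to 0.444, from 0.445 to 0.458 and from 0.463 to 0.487.

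Finally, the article gives no reason for stratifying on distress, so the choice of stratum is not evidence that distress is strongly prognostic.

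**Conclusion.** The point holds as a minor efficiency improvement to the ANCOVAs. On the natural reading of the plan, a score already held for every patient is reduced to two levels in models that have no baseline outcome value. Under a near-normal score, a linear relation and a 30% to 50% high stratum, that gives up about 36% to 42% of what distress could explain. The consequence is about 0 to 4 points of power at 45 per group over correlations of 0.1 to 0.5, with no net gain below about 0.2. It would be wrong to read this as bias, as an invalid analysis or as a shortfall in the planned power. The article supports none of these.

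**What to change.** In Statistical methods, state that the ANCOVA models keep the low/high stratum indicator and add the pre-randomisation 0-10 distress score as a linear covariate. Keeping the indicator leaves the analysis faithful to the randomisation, and the same sentence removes the doubt about coding. No new data are needed. The cost is one degree of freedom and a negligible loss of precision (about 1% of the treatment-effect variance) if distress turns out to be unrelated to the outcome. The change should be fixed before outcome data are examined. No gain in precision should be claimed for the logistic co-medication model.
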